### Statistical analysis

Outcome analyses will be undertaken on an intention-to-treat basis. Data will be presented as means ± SD. The Kolmogorov-Smirnov goodness-of-fit test will be used to test for normal distribution, and data not normally distributed will be log-transformed. Correlation analyses will be performed using the Pearson correlation coefficient. Significance of changes during the study will be assessed by comparing change of means between placebo and prebiotic treatment periods by paired sample t-tests. Trial data will be analysed using a linear mixed model design based on repeated measures to account for fixed factors such as treatment sequence (inulin – placebo vs placebo - inulin) and treatment period (intervention 1 vs intervention 2) in addition to participants as a random factor. Significant differences will be defined as a value of P < 0.05 based on two-sided tests. Any differences in physical activity levels, anthropometry, energy or nutrient intake during the course of the trial will be identified using ANOVA. Gastrointestinal symptom data obtained by visual analogue scale will be analysed using the Wilcoxon signed rank test. Effect sizes including 95% confidence intervals will be calculated for all significant outcomes. Data analysis will be performed using SPSS 20.0 software (SPSS, Chicago, IL).

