### Sample size calculation

The minimum difference we wish to detect is 0.4 micromol/L serum CML (20% reduction in CML), with a standard deviation of 0.4 [39] with 5% Significance and 80% Power. This calculates as a total sample size of 18 individuals, plus 12 individuals to allow for withdrawals = 30 subjects required. Epidemiological studies have demonstrated a positive correlation between serum CML and all-cause and cardiovascular mortality, cardiovascular disease, glucose intolerance, impaired insulin secretion, renal impairment and diabetic vascular complications [40,41]. A 0.4 micromol/L increase in serum CML concentration represented a 68% increased risk for all-cause mortality over seven years in a large prospective cohort study [42].

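### Two unranked analyses are given for the prebiotic–placebo difference; the paired t-test uses only participants with both periods and leaves out period, so the mixed model should be named as the single primary analysis

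*Protocol article*

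**What the plan says.** The Statistical analysis section of the protocol article opens with "Outcome analyses will be undertaken on an intention-to-treat basis". It then gives two methods for comparing the supplements, in consecutive sentences:

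- The first is the stated way of judging significance, namely "comparing change of means between placebo and prebiotic treatment periods by paired sample t-tests". This sentence names no term for period or sequence.
- The second is a model, introduced by "Trial data will be analysed using a linear mixed model design based on repeated measures to account for fixed factors such as treatment sequence"; further on, the same sentence adds "treatment period (intervention 1 vs intervention 2) in addition to participants as a random factor".

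One threshold covers both: "Significant differences will be defined as a value of P < 0.05 based on two-sided tests". Neither method is called primary or supportive, and neither is assigned to particular outcomes. The section mentions no imputation.

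Two other sections matter here. The Sample size calculation arrives at 18 participants, "plus 12 individuals to allow for withdrawals = 30 subjects required". Outcome measurements defines the primary outcome as the difference between treatments in two serum markers, CML and MG.

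**The concern.** Both methods test the same hypothesis, and on the same data they can give different P values. With incomplete data they can also give different estimates. With no ranking, the choice can be made after both results are known. Read literally, the sentence on significance gives the decision to the t-test, which is the weaker of the two for this design.

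The t-test has two separate weaknesses:

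1. **Who is analysed.** It needs a value from each period. A participant who completes period 1 and then leaves contributes nothing, which sits badly with an intention-to-treat statement when the plan allows for losing 12 of 30.
2. **Period.** It has no period term. A shift between the two periods inflates the error variance. If completers are unequal between sequences, the shift also moves the estimate.

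The first concerns the analysis population. The second concerns bias and precision and is not an intention-to-treat issue.

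**Working it through.** **Inputs from the protocol article.** Target difference 0.4 micromol/L CML, SD 0.4 (type not stated), 5% significance, 80% power, 18 evaluable, 12 added for withdrawals, 30 randomised.

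**Assumptions of this check.** Equal allocation to sequence; SD 0.4 is the within-person SD of a single measurement; period shifts of 0.2 and 0.4 micromol/L; completers split 9/9 or 11/7. The article gives no period effect and no completer split.

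**Step 1: reproduce the 18.** SD of the within-person difference = 0.4 × √2 = 0.566. With n = 18, SE = 0.566/√18 = 0.133 and the noncentrality is 0.4/0.133 = 3.0. Two-sided noncentral-t power is 0.807 on 17 df (paired t-test) and 0.804 on 16 df (period fitted). With 17 participants both fall below 0.80 (0.781 and 0.778). So 18 is reproduced under either analysis.

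**Step 2: who is analysed.** If all 12 allowed withdrawals occur and none leaves a second-period value, the t-test uses 18/30 = 60% of those randomised.

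To see what partial data add, suppose all 12 give a period 1 value, six in each sequence. Let the total SD be 0.4 and the within-person correlation be ρ. With treatment, period and sequence fitted and variances known:

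- Completers only: SE² = 0.16 × ½ × 2(1−ρ)/9.
- With partial data: SE² = 0.16 × ½ × [(1−ρ²)/9 + (1−ρ)²/15].

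| ρ (assumed) | SE, 18 completers | SE, 18 + 12 partial |
|---|---|---|
| 0 | 0.133 | 0.119 |
| 0.5 | 0.094 | 0.089 |
| 0.7 | 0.073 | 0.071 |

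The precision gain is modest and shrinks as ρ rises. The main benefit is keeping randomised participants in the analysis.

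**Step 3: period shift with completers split 9/9.** Let the period shift be p and the treatment effect d. The expected difference between treatments is d − p in one sequence and d + p in the other. The mean is unbiased, but the spread between sequences enters the t-test's error term. Simulated power with d = 0.4:

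| Shift p | Paired t-test | Period fitted | Trials where the verdicts differ |
|---|---|---|---|
| 0 | 0.81 | 0.80 | 2% |
| 0.2 | 0.77 | 0.80 | 4% |
| 0.4 | 0.65 | 0.80 | 15% |

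**Step 4: completers split 11/7.** Bias of the paired mean = p × (11 − 7)/18 = 0.22p. That is 0.044 micromol/L for p = 0.2 and 0.089 for p = 0.4, against a target of 0.4.

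With period fitted, SE = (0.566/2) × √(1/11 + 1/7) = 0.137, and power is about 0.78. When the bias opposes the effect, paired power is 0.67 (p = 0.2) and 0.42 (p = 0.4), and the two tests disagree in 13% and 36% of simulated trials. When the bias favours the effect, paired power is about 0.85 for both shifts, partly because the estimate is exaggerated.

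**The case against.** Much can be said for the plan, and some of it stands.

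- **The plan as a whole does not ignore period.** The mixed-model sentence includes period and sequence; only the t-test omits them. With complete data and equal sequences the two point estimates coincide. Both points are correct.
- **The intention-to-treat conflict is conditional.** It depends on missing values not being imputed, and handling of missing data is commonly left to a fuller document that is not shown here. Twelve of 30 is an allowance, not a forecast. A reader might infer an outright contradiction, or that 40% will be lost; the article supports neither. What stands is that a paired t-test on observed values cannot deliver the stated basis.
- **Gastrointestinal effects of the fibre do not by themselves cause the bias.** A reader might infer that withdrawals on inulin make the completers unequal. Both sequences take the fibre once, so withdrawal that depends only on the supplement gives equal expected completion. Imbalance needs chance, or withdrawal that depends on period or sequence.
- **False positives are not generally inflated.** With no treatment effect, the paired test's type I error is 0.039 and 0.017 at 9/9, and 0.049 and 0.043 at 11/7, for shifts of 0.2 and 0.4. It rises above 5% only with a stronger imbalance, for example 0.064 and 0.083 at 12/6.
- **The mixed model cannot be said to lack a treatment term.** The sentence introduces its factors as examples, so the list is not exhaustive.
- **The shifts are assumed.** A shift of 0.4 equals the whole target effect and is an extreme case.

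None of this ranks the two tests.

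**Conclusion.** The point holds in this form: the article gives two unranked tests of the primary contrast, and the one said to assess significance is a completers-only test without a period term.

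The size depends on assumptions. With no period shift and balanced completers the choice is nearly immaterial (0.807 against 0.804). With balanced completers, an assumed shift of 0.2 costs the t-test about 3 percentage points of power, and a shift of 0.4 about 15. At an assumed 11/7 split the t-test also carries a bias of 22% of the shift, while the period-adjusted analysis stays unbiased by period with power of about 0.78. All of these figures rest on reading SD 0.4 as within-person, which reproduces the stated 18. The conflict with the intention-to-treat statement rests on missing values not being imputed.

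**What to change.** In the Statistical analysis section, name one primary analysis for each primary marker (CML and MG): the linear mixed model of end-of-period values, with treatment, period and sequence as fixed effects and participant as a random effect. Include all randomised participants with at least one end-of-period value. State that the treatment coefficient, with its 95% confidence interval and P value, is the primary result. Writing the treatment term out is a clarification only.

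Delete the paired t-test sentence, or keep the test labelled as a completers-only sensitivity analysis.

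The cost is wording and one error degree of freedom: power at n = 18 goes from 0.807 to 0.804, and the required evaluable number stays at 18. One limit remains. Samples are taken only at baseline and at the end of each period, so anyone who leaves before an end-of-period sample is unanalysed under either method. The text should say so, rather than let the intention-to-treat label imply otherwise.

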## Abstract

**Background:**

Advanced glycation endproducts (AGEs) contribute to the development of vascular complications of diabetes and have been recently implicated in the pathogenesis of diabetes. Since AGEs are generated within foodstuffs upon food processing, it is increasingly recognised that the modern diet is replete with AGEs. AGEs are thought to stimulate chronic low-grade inflammation and promote oxidative stress and have been linked to the development of insulin resistance. Simple therapeutic strategies targeted at attenuating the progression of chronic low-grade inflammation and insulin resistance are urgently required to prevent or slow the development of type 2 diabetes in susceptible individuals. Dietary modulation of the human colonic microbiota has been shown to confer a number of health benefits to the host, but its effect on advanced glycation is unknown. The aim of this article is to describe the methodology of a double-blind placebo-controlled randomised crossover trial designed to determine the effect of 12 week consumption of a prebiotic dietary supplement on the advanced glycation pathway, insulin sensitivity and chronic low-grade inflammation in adults with pre-diabetes.

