### Outcome measurements

The primary outcome of interest is the difference in serum AGE and AGE-precursor concentration (measured as CML and MG respectively) between experimental and control treatments. Secondary outcomes include HbA1c, insulin resistance (measured indirectly by homeostasis model assessment), antioxidant capacity (reduced glutathione), markers of oxidative stress on lipid molecules (urinary 8-isoprostanes), inflammatory biomarkers (serum IL-6, high sensitivity C-reactive protein, MCP-1, sRAGE), adhesion molecules (E-selectin), gut barrier integrity (TLR4), 24-hour urine and faecal CML and MG concentrations, faecal bacterial composition (*Bifidobacterium* spp., *Lactobacillus* spp., *Roseburia* spp., *Faecalibacterium prausnitzii* and *Akkermansia muciniphila*) and faecal short chain fatty acid concentrations. Lipid levels (serum total cholesterol, LDL, HDL, TG) and blood pressure will also be measured. Anthropometric measurements including BMI and waist circumference will be collected, in addition to comprehensive dietary and lifestyle data. Gastrointestinal side-effects will be assessed using a visual analogue scale adapted from Lecerf *et al.*[45]. The scale rates nine items including flatulence, bloating, rumbling, abdominal cramps, a global digestive tolerance score calculated from the five previous items, stool consistency, stool frequency and general well-being through disturbances in usual and professional activities as well as disturbances in personal and social activities. Items are scored on a 10 cm linear scale.

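### One unadjusted P < 0.05 rule covers at least 20 secondary outcomes and decides which get confidence intervals; secondary results should be labelled exploratory, with intervals for all

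*Protocol article*

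**What the plan says.** The Statistical analysis section gives a single criterion: "Significant differences will be defined as a value of P < 0.05 based on two-sided tests". Nothing limits it to the primary outcome. The same section promises effect sizes and 95% confidence intervals for outcomes found significant and does not promise them for the rest, which are covered only by the general statement that data appear as means with SD. It also plans Pearson correlations, which fall under the same threshold.

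Outcome measurements separates two levels. The primary is serum CML and MG: "The primary outcome of interest is the difference in serum AGE and AGE-precursor concentration (measured as CML and MG respectively"). The secondary list opens with "Secondary outcomes include HbA1c, insulin resistance (measured indirectly by homeostasis model assessment), antioxidant capacity (reduced glutathione") and goes on through urinary 8-isoprostanes, then "inflammatory biomarkers (serum IL-6, high sensitivity C-reactive protein, MCP-1, sRAGE), adhesion molecules (E-selectin), gut barrier integrity (TLR4"), then urine and faecal CML and MG, five bacterial groups and faecal short-chain fatty acids (SCFA). Lipids and blood pressure are also measured, and the abstract lists both as secondary.

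The abstract's Background says the trial is designed to determine the effect "on the advanced glycation pathway, insulin sensitivity and chronic low-grade inflammation in adults with pre-diabetes". The title names the same three areas. The sample size rests on serum CML alone.

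**The concern.** Two of the three areas in the stated aim, insulin sensitivity and inflammation, are addressed only by secondary outcomes. Inflammation is represented by four named biomarkers, or six if E-selectin and TLR4 are included, and none is designated as the one that decides. Under the rule as published, a P-value below 0.05 on any of them is a significant difference and could be reported as an effect on inflammation.

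The promise about confidence intervals adds to this. Results that cross the threshold, including chance ones, would carry an effect size and interval. Results that do not cross it need not, so a reader could not tell whether a null marker excludes a useful effect or is merely imprecise. With 18 evaluable participants planned and 30 enrolled, many of these estimates may be imprecise.

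**Working it through.** **The plan's own figure.** The inputs in Sample size calculation are a CML difference of 0.4 micromol/L, an SD of 0.4, a 5% level and 80% power. From these the article concludes: "This calculates as a total sample size of 18 individuals, plus 12 individuals to allow for withdrawals = 30 subjects required". Take 0.4 as the SD of a single measurement and assume no within-person correlation. The SD of the paired difference is then 0.4 × √2 = 0.566. The normal approximation gives (1.960 + 0.842)² × 0.566² / 0.4² = 15.7, so 16. The paired t-test needs 18 (power 0.781 at n = 17, 0.807 at n = 18). The stated 18 reproduces for CML. It says nothing about the secondary outcomes and is unaffected by this point.

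**Counting the secondary tests** (Outcome measurements):
- HbA1c, HOMA, glutathione: 3
- urinary 8-isoprostanes: 1
- IL-6, hsCRP, MCP-1, sRAGE: 4
- E-selectin, TLR4: 2
- CML and MG in urine and faeces: 4
- five bacterial groups: 5
- SCFA, counted once: 1

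The total is 20. Four lipids, and blood pressure as one or two tests, make it 25 or 26. The count leaves out adiponectin and myeloperoxidase (in the abstract's list), the gastrointestinal scale, anthropometry and the correlations.

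**Error rates if no secondary outcome is affected.** For k independent tests at two-sided 5%:
- at least one false result in either direction: 1 − 0.95^k
- at least one in the favourable direction: 1 − 0.975^k

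For k = 20 these are 1 − 0.95^20 = 0.642 and 1 − 0.975^20 = 0.397. The expected number of false results is 20 × 0.05 = 1.0, whatever the correlation.

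The article gives no correlations between outcomes, so a common correlation ρ between test statistics is assumed, with all outcomes signed so that favourable points the same way. With z = 1.960 and C standard normal, the either-direction probability is 1 − E{[Φ((z − √ρ·C)/√(1−ρ)) − Φ((−z − √ρ·C)/√(1−ρ))]^k}. The favourable-direction version drops the second Φ term. Numerical integration gives:

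| Tests | Direction | ρ = 0 | ρ = 0.5 | ρ = 0.8 |
|---|---|---|---|---|
| 20 listed secondaries | either | 64% | 42% | 22% |
| 20 listed secondaries | favourable | 40% | 21% | 11% |
| 26 with lipids and two blood pressures | either | 74% | 48% | 24% |
| 14, without bacteria and SCFA | either | 51% | 35% | 20% |
| 6 inflammation-related markers | either | 26% | 21% | 14% |
| 6 inflammation-related markers | favourable | 14% | 10% | 7% |
| 4 inflammatory biomarkers | either | 19% | 16% | 11% |
| 4 inflammatory biomarkers | favourable | 10% | 8% | 6% |

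**The case against.** The strongest reply is that the article already ranks its outcomes. Serum CML and MG are primary, the rest are labelled secondary, power is computed on CML alone, and no sentence rests trial success on a secondary outcome. The end of the Background also says the trial will explore changes in gut microbiota, which is exploratory wording for the bacteria and arguably for SCFA. A hierarchy or adjustment among secondaries is commonly left to an analysis plan, so its absence from a journal article is not an error. All of this stands. What remains is text the article does contain: a threshold with no stated limit, and intervals tied to passing it. An analysis plan that treated the secondaries as exploratory would have to override that text.

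Three stronger readings are tempting, and the documents do not support them.
- A reader might infer that an inert supplement would probably show a secondary benefit. It would not. The favourable-direction chance for 20 tests is at most 40%, and even the either-direction chance falls below one half by ρ = 0.5.
- A reader might infer that the aim asserts effects on insulin sensitivity and inflammation. It says only that the trial will determine the effect.
- A reader might apply the all-null assumption to the whole list. The Intervention section cites earlier evidence of a bifidogenic effect of inulin, so the bacterial outcomes may well not be null. The 14-test row is the fairer figure for the remaining outcomes.

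**Conclusion.** The point holds as a matter of how secondary results may be claimed and reported. Applied as written, the rule carries a 22% to 64% chance of at least one false significant result in either direction among the 20 listed secondaries, and 11% to 40% in the favourable direction. Without bacteria and SCFA it is 20% to 51% in either direction. For inflammation alone, with four to six markers, it is about 11% to 26% in either direction and roughly half that in the favourable direction.

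These ranges assume that every null in the set is true and that the tests share one correlation between 0 and 0.8. That correlation is an assumption and does not come from the article. Across the whole range, the chance of some false result in either direction is more than twice the 5% that the threshold suggests. The primary comparison and the sample size are untouched. How the two primary markers share the error rate is a separate question not addressed here.

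**What to change.** In the Statistical analysis section:
- State that a claim of significance at two-sided P < 0.05 applies to the primary analysis only.
- State that all secondary outcomes and the Pearson correlations are exploratory and that their P-values are nominal.
- Report effect estimates with 95% confidence intervals for every outcome, whether or not it is significant.

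If the sponsor wants a firmer conclusion on insulin sensitivity or inflammation, it can go further. It would name in advance one deciding marker for each and specify how multiplicity is controlled. The choice of marker is the sponsor's, and nothing in the article favours one.

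The cost is a few sentences and some additional intervals in the results tables, with no new data, visits or participants. The downside is that an isolated secondary P < 0.05 could no longer be presented as a demonstrated effect.

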**Methods/Design:**

Thirty adults with pre-diabetes (Impaired Glucose Tolerance or Impaired Fasting Glucose) aged between 40–60 years will be randomly assigned to receive either 10 grams of prebiotic (inulin/oligofructose) daily or 10 grams placebo (maltodextrin) daily for 12 weeks. After a 2-week washout period, study subjects will crossover to receive the alternative dietary treatment for 12 weeks. The primary outcome is the difference in markers of the advanced glycation pathway carboxymethyllysine (CML) and methylglyoxal (MG) between experimental and control treatments. Secondary outcomes include HbA_1c_, insulin sensitivity, lipid levels, blood pressure, serum glutathione, adiponectin, IL-6, E-selectin, myeloperoxidase, C-reactive protein, Toll-like Receptor 4 (TLR4), soluble receptor for AGE (sRAGE), urinary 8-isoprostanes, faecal bacterial composition and short chain fatty acid profile. Anthropometric measures including BMI and waist circumference will be collected in addition to comprehensive dietary and lifestyle data.

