## Data collection

### Dietary intake

An experienced research dietitian will obtain a comprehensive dietary history from each study participant at baseline and at the completion of each intervention period. A dietary history is a structured interview method consisting of questions regarding habitual food intake. It involves a 24-hour diet recall followed by a food frequency questionnaire to clarify information about usual consumption over the previous month. Usual portion sizes will be obtained in household measures and with the use of photographic aids. The dietitian will review the dietary history with each participant, probing for details on portion sizes and cooking methods in order to improve data accuracy. Dietary AGE content will be estimated from an open source database which lists the AGE concentration of foods using validated analytical techniques [46]. Dietary macro and micronutrient intakes will be estimated using the Foodworks nutrient software program (Xyris Software, NSW, Australia). Each participant will also be randomly contacted by telephone during the study and asked to provide a 24-hour diet recall, and changes in urinary urea excretion will be monitored in order to validate the dietary history data collected [47]. Physical activity will be estimated by asking participants to complete the International Physical Activity Questionnaire (Short Form) prior to and at the completion of experimental and placebo intervention periods [48].

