### Promotion of weight reduction

An energy-restricted diet resulting in weight loss has been shown to reduce serum AGE levels in overweight and obese individuals [94]. The consumption of prebiotics in human clinical trials has promoted self-reported satiety [95], weight reduction, reduced production of the orexigenic hormone grehlin and stimulated expression of the appetite-reducing hormone peptide YY (PYY) [96]. Interaction with GPR41 by the SCFAs proprionate and butyrate increases satiety [97], upregulates PYY production and modulates the expression of leptin, a hormone important in controlling energy intake and expenditure [31].

In mice, the selective growth of certain lactobacillus species in the colon reduced body fat storage through the up-regulation of fiaf (fasting induced adipose factor) gene expression and inhibition of lipoprotein lipase (LPL) [98-100]. These findings may have the potential to affect weight reduction in humans and subsequently reduce circulating AGE levels.

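### The ANOVA for weight, diet and activity names neither treatment as its factor nor a within-participant comparison, and on most readings it would miss an inulin–placebo difference

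*Protocol article*

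**What the plan says.** The Statistical analysis section contains three relevant statements.

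- Changes are to be assessed by "comparing change of means between placebo and prebiotic treatment periods by paired sample t-tests".
- A model is then given: "Trial data will be analysed using a linear mixed model design based on repeated measures to account for fixed factors such as treatment sequence". Period is the other fixed factor mentioned, and participant is random.
- Activity, anthropometry and intake then get a sentence of their own: "Any differences in physical activity levels, anthropometry, energy or nutrient intake during the course of the trial will be identified using ANOVA".

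The first two statements refer to treatment periods, sequence or period. The third refers only to time.

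The design is a two-period crossover in which, after washout, "study subjects will crossover to receive the alternative dietary treatment for 12 weeks". Diet is recorded "at baseline and at the completion of each intervention period". The Baseline assessment and Follow up visits sections put anthropometry at the same three times. The activity questionnaire is scheduled "prior to and at the completion of experimental and placebo intervention periods".

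The Intervention section asks participants to keep their usual diet and activity. The discussion offers weight loss as one route to lower AGEs: "An energy-restricted diet resulting in weight loss has been shown to reduce serum AGE levels in overweight and obese individuals".

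**The concern.** This analysis is the plan's check on whether weight, diet or activity differed between the supplements. The relevant contrast is inulin against placebo within the same person. The sentence describes a comparison over the trial's duration, and its most natural reading is a comparison of visits. In a crossover, visit and treatment are different things: at either follow-up, one sequence has just finished inulin and the other has just finished placebo.

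The danger is false reassurance. A non-significant result from a test that could hardly detect a treatment difference would invite the statement that weight and diet did not differ. A CML effect could then be described as independent of them. The anthropometric results, which the article lists among its outcome measurements, would also be under-analysed in their own right.

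**Working it through.** **The plan's own figure.** The article gives no power or variance for these variables. Its only sample-size figure is for CML. Taking 0.4 as the within-participant SD, the SD of the difference is 0.4 × √2 = 0.566, and 18 participants give 80.4% power for a difference of 0.4. Allowing for withdrawals, 18/(1 − 0.40) = 30. Both stated numbers reproduce, and neither depends on this point.

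**Mixing by visit.** Let inulin shift a variable by δ relative to baseline and to placebo, with equal sequences and no period effect. Measured from baseline, the visit means are 0, δ/2 and δ/2, while the condition means (baseline, inulin, placebo) are 0, δ and 0. The two follow-up visits do not differ at all. The between-level sum of squares is n·Σ(mean − grand mean)². With n = 30 and δ = 0.3 SD:

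- By visit: 30 × (0.10² + 0.05² + 0.05²) = 0.45.
- By condition: 30 × (0.20² + 0.10² + 0.10²) = 1.80.

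Grouping by visit keeps a quarter of the signal and moves the rest into the error term.

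**Ignoring the pairing.** A one-way ANOVA by condition uses the total variance (1, in SD units) as error. Its expected between-condition mean square is 1.80/2 + (1 − ρ), which is 1.0 at ρ = 0.9 and 1.2 at ρ = 0.7. The 5% critical value of F on 2 and 87 degrees of freedom is about 3.1, so rejection is rare. Run by visit, the one-way ANOVA has a quarter of that signal against the same error.

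**The crossover contrast.** Its noncentrality is δ√n / √(2(1 − ρ)):

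- ρ = 0.9: 0.3 × 5.477 / 0.447 = 3.67, power about 94%.
- ρ = 0.7: 0.3 × 5.477 / 0.775 = 2.12, power about 53%.

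**Simulation** (assumed: n = 30, 15 per sequence, δ = 0.3 SD, two-sided 5%):

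| Reading of the sentence | ρ = 0.7 | ρ = 0.9 |
|---|---|---|
| Repeated-measures ANOVA by visit | 15% | 34% |
| Ordinary one-way ANOVA by condition | 4% | 0.4% |
| Repeated-measures ANOVA by condition | 56% | about 96% |
| Crossover contrast (period removed) | 53% | 94% |

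**A second parameterisation** (within-participant SD 1, between-participant SD 3, shifts of 0.5, 0.707 and 1.0 within-participant SD):

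| Analysis | N = 18 | N = 30 |
|---|---|---|
| Repeated measures, three visits | 9 / 13 / 20% | 13 / 21 / 36% |
| Repeated measures, two follow-up visits | 4 / 3 / 2% | 4 / 3 / 2% |
| Repeated measures by condition | 30 / 54 / 85% | 48 / 80 / 98% |
| Paired inulin–placebo test | 29 / 51 / 81% | 47 / 76 / 96% |

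With the two follow-up visits alone, a real shift is flagged less often than the nominal 5%.

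**The case against.** The strongest objection is that the article never names the factor. An ANOVA over baseline, inulin and placebo also fits the sentence. Run as repeated measures, it has about the same power as the paired test and mixes nothing. The activity questionnaire is scheduled by experimental and placebo period, which points towards a treatment comparison. The mixed-model sentence refers to trial data in general and does not exclude these variables. The article is also a condensed account, and a fuller analysis plan may settle the matter.

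Much of this stands. A reader might infer that the plan definitely pools the two supplements at every visit. The text does not support that: the factor is open, and nobody is on either supplement at baseline. Nor does it say that the ANOVA ignores repeated measurement. The percentages are illustrations under assumed variances.

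The objection does not remove the point. This is more than detail left out. The article commits these variables to a separate method, in time-based wording, beside two sentences that do use the crossover structure. Of the four combinations (visit or condition, ordinary or repeated measures), only one performs adequately, and it takes no account of period.

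**Conclusion.** The point holds as a weakness in how a secondary analysis is fixed. As worded, the ANOVA leans towards a comparison of visits that would largely cancel an inulin–placebo difference, and it does not exclude an ordinary one-way analysis that would hide one. Under the assumed 0.3 SD effect with 30 participants and correlation 0.7 to 0.9, the loss is from 53–94% detection to 15–34% by visit, or to 4% or less with a one-way ANOVA. The direction follows from the design. The size depends on variances that the article does not give.

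Two further inferences are not supported:

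- A reader might conclude that an undetected weight change would bias the CML result. It would not. A weight change caused by inulin lies on the causal path that the article itself proposes, so it is a mediator, and the randomised comparison remains valid. Only the explanation of an effect is at risk.
- A reader might extend the criticism to the symptom scales ("Gastrointestinal symptom data obtained by visual analogue scale will be analysed using the Wilcoxon signed rank test"). That test is already paired. The bowel adaptation described under Intervention occurs within a treatment period and gives no reason to expect a difference between periods.

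**What to change.** Replace the ANOVA sentence. State that physical activity, anthropometry, energy and nutrient intake will be analysed with the linear mixed model already described in the Statistical analysis section, with treatment, period and sequence as fixed factors and participant as a random factor. Name treatment explicitly. Report the inulin–placebo difference with its 95% confidence interval for each variable, whether or not it is significant, so that readers can see how large a difference the data leave open. If a comparison of visits is also wanted to describe drift over the trial, label it as that and do not use it as evidence that the supplements were alike.

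The cost is one sentence of wording. No new data, visits or participants are needed.
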